### MRI interpretation in ART-Pro-1

3.5

MRI examinations are evaluated by two expert radiologists at the imaging center, with each radiologist interpreting approximately half of the cases in the role of reader 1 and half in the role of reader 2 (either by random assignment or by which radiologist happens to be on clinical service the day the patient is scanned). Reporting of MRI examinations is done as the per PI-RADS v2.1 guidelines. Both readers also assess the quality of each modality reviewed (T2W, DWI, and DCE). Both readers know the clinical indication for the prostate MRI examination given by the ordering physician. Both also have access to the patient’s electronic medical record for age, race, ethnicity, family history, prostate-specific antigen level, prior biopsy information, etc. Both readers record whatever clinical information they reviewed by copying it into their research reports in our centralized REDCap database.

#### Reader 1

3.5.1

Reader 1 fills out a research report (Reader 1 Report; see the Supplementary material), captured and stored in our centralized REDCap database, of the MRI findings. Reader 1 is first blinded to the DCE sequence and reports the MRI using only the biparametric (T2W and DWI) sequences. After reporting the bpMRI, reader 1 is unblinded to the DCE sequence and re-reports the MRI using the full mpMRI (T2W, DWI, and DCE) sequences. Reader 1 cannot go back and change his/her response for own bpMRI findings, so reader 1 ultimately provides two research reads: one without DCE and one with DCE. For both the bpMRI and mpMRI reports, reader 1 provides an overall estimate of the probability of csPCa per lesion and per patient.

#### Reader 2

3.5.2

While blinded to the findings of reader 1, reader 2 completes a separate research report using bpMRI and RSIrs (Reader 2 Report; see the Supplementary material), captured and stored in our centralized REDCap database. Lesions are assessed according to PI-RADS v2.1 with bpMRI; additionally, reader 2 reports the maximum RSIrs for each lesion. Reader 2 also provides an overall estimate of the probability of csPCa per lesion and per patient.

As described above, RSIrs images in ART-Pro are acquired in two opposite phase encoding directions to permit multi-*b*-value correction of distortion due to *B_0_* field inhomogeneity. Both readers are asked to indicate whether DWI is distorted significantly in each examination. If there is significant distortion in standard DWI, reader 2 also reports whether the distortion is meaningfully reduced in distortion-corrected RSI.

#### Re-evaluation

3.5.3

Once both readers have completed their separate research reports, reader 2’s report is delivered to reader 1, the clinical radiologist of record. Upon review of reader 2’s report and after any warranted discussion with reader 2, reader 1 has the opportunity to update their interpretation after considering reader 2’s findings. Reader 1 fills out a second research report (Re-Evaluation Report; see the Supplementary material), captured and stored in our centralized REDCap database, indicating whether the reader would like to make any changes to the initial report. Reader 1 then submits a final clinical report to the patient’s electronic medical record.

#### Clinical outcomes

3.5.4

As a pragmatic study, biopsy recommendations and other clinical decisions are left to the discretion of the patient’s medical team as per clinical routine. We will review patient medical records to extract relevant outcomes, including whether a biopsy was recommended, whether a biopsy was performed (including technique), and the outcome of any biopsy: number of systematic cores and their locations, number of targeted cores and the corresponding target location, Gleason score and percentage of Gleason patterns per core, ductal or acinar type for any carcinoma, presence of cribriform pattern, presence of intraductal carcinoma, and presence of perineural invasion. If clinical interpretation includes notes of other poor prognostic pathology features, we will also record these [38]. If clinical genomic, pathomic, or other tests are performed on the tumor specimen (eg, Decipher and Artera), we will record these results. If the patient undergoes radical prostatectomy, the final pathology will be recorded, including Gleason score, percentage of Gleason patterns, perineural invasion, tumor features (acinar, ductal, intraductal carcinoma, and cribriform pattern), extraprostatic extension, seminal vesicle invasion, etc.

### Study schema for ART-Pro-2

3.6

A schematic presentation of ART-Pro-2 is provided in Figure 2.

**Fig. 2 f0010:**
[figure not shown]
In ART-Pro-2, radiologists of different levels of experience (novice, basic, and expert according to the ESUR/ESUI criteria) evaluate patient images from ART-Pro-1. For patient cases where they are assigned to multiparametric MRI (mpMRI; left), the radiologists provide a report using only biparametric MRI (bpMRI; no contrast) and then a second report after reviewing the dynamic contrast-enhanced images (full mpMRI). For patient cases where they are assigned to Restriction Spectrum Imaging restriction score (RSIrs) plus mpMRI (right), the radiologists provide three reports, in the following order, based only on: (1) axial *T_2_*-weighted (T2W) images and RSIrs maps, (2) bpMRI plus RSIrs maps, and (3) full mpMRI plus RSIrs maps. ESUI = European Association of Urology Section of Urological Imaging; ESUR = European Society of Urogenital Radiologists; MRI = magnetic resonance imaging; w/ = with; w/o = without.

### MRI interpretation in ART-Pro-2

3.7

ART-Pro-2 will be conducted retrospectively and will not impact patient care. Radiologists will be categorized by level of experience for prostate MRI based on the joint European Society of Urogenital Radiologists (ESUR) and the EAU Section of Urological Imaging (ESUI) criteria: novice prostate radiologists defined as having read <400 cases, basic prostate radiologists defined as having read ≥400 and <1000 cases, and expert prostate radiologists defined as having read ≥1000 cases [11]. The design of ART-Pro-2 in evaluating nonexpert readers retrospectively allows for “locking” of reader experience level, whereas if evaluated over the ART-Pro-1 trial period, readers could change (by criteria) from being novice to basic and/or expert. Each radiologist will be provided a list of 100 patient cases to review, 50 with mpMRI and 50 with RSIrs plus mpMRI. Case lists will be generated as random permutations of cases while requiring that (1) no radiologist be assigned cases from the institution where he/she works (to ensure that the radiologist has not seen the cases before), (2) each patient case is assigned to at least three radiologists as mpMRI (one from each of the experience levels), and (3) each patient case is assigned to at least three (different) radiologists (one from each of the experience levels) as RSIrs plus mpMRI. Thus, each patient case will be reviewed by six radiologists (two from each of the experience levels). Image sets will be provided as sessions using the MIM Zero Footprint platform (MIM Software, Cleveland, OH, USA) to facilitate individual work lists and presentation of image subsets.

#### Multiparametric MRI patient cases

3.7.1

For mpMRI patient cases, the radiologist will first be presented with bpMRI images and will complete a REDCap report with own findings according to PI-RADS v2.1. The radiologist will then proceed to review the DCE images for the case and will complete a second REDCap report according to PI-RADS v2.1. In each report, the radiologist will provide an estimate of the probability of csPCa per lesion and per patient.

#### RSIrs plus mpMRI patient cases

3.7.2

For RSIrs plus mpMRI patient cases, the radiologist will first be presented with only RSIrs maps and axial T2W images. The radiologist will complete a REDCap report based only on images from these two series. As PI-RADS does not apply to RSIrs plus axial T2W images, these reports will use the 5-point Likert scale used in the PROMIS trial: highly unlikely (1), unlikely (2), equivocal (3), likely (4), or highly likely (5). The radiologist will then proceed to review the full bpMRI image set (ie, adding conventional DWI and ADC) and will complete a second REDCap report according to PI-RADS v2.1 guidelines. Finally, the radiologist will review DCE images and complete a third REDCap report for mpMRI according to PI-RADS v2.1. In each report, the radiologist will provide an estimate of the probability of csPCa per lesion and per patient.

## Statistical analysis

4

We expect bpMRI to be noninferior to mpMRI among expert radiologists for the detection of csPCa and avoidance of unnecessary biopsies. We expect that expert radiologists will have superior performance to nonexperts with bpMRI and with mpMRI. However, we hypothesize that adding RSIrs to bpMRI will facilitate objective MRI interpretation so that nonexpert radiologists using RSIrs plus bpMRI will have noninferior performance to experts using bpMRI or mpMRI. We expect that RSIrs as a stand-alone quantitative biomarker will be noninferior to qualitative mpMRI for discriminating patients with csPCa from those without csPCa.

### Analyses for ART-Pro-1

4.1

#### Statistical analysis plan for primary and key secondary objectives

4.1.1

An exploratory data analysis will be conducted, and visualization tools, including the scatterplot, boxplot, and histogram, will be used to examine the data and potential missingness [39]. For all tests below, the significance level of 0.05 will be used in the statistical testing. All analyses will be conducted using software R 4.3.1.

For examining the noninferiority of bpMRI versus mpMRI for the detection of csPCa, we will conduct one-sided noninferiority tests of correlated proportions, to examine the sensitivity and specificity of the following paired readings: reader 1 bpMRI versus reader 1 mpMRI and reader 2 bpMRI versus reader 1 mpMRI. For both paired comparisons, the outcome of each reading for each patient is the binary result of positive or negative MRI. A McNemar's test will be used to test the null hypothesis that the differences in the probabilities (% of second test minus % of the first test) of positive MRI (for testing on sensitivity) and negative MRI (for testing on specificity) from the two readings in the paired comparison are larger than the predetermined noninferiority margins [40]. The *p* values will be reported for all tests.

For examining the noninferiority of RSIrs versus mpMRI, we will compare the areas under the receiver operating characteristic (ROC) curve (AUCs) of using RSIrs (continuous variable) to predict the binary outcome of csPCa versus using mpMRI (ordinal categorical variable; treat like continuous variable) to predict the outcome [41]. A noninferiority test will be conducted to compare the two ROC curves associated with the two predictors at significance level 0.05.

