### Objectives

2.2

The primary and secondary objectives are listed in Table 1.

**Table 1 t0005:** Study objectives

*Primary objectives*
1. Evaluate if bpMRI is noninferior to mpMRI among expert (ART-Pro-1) and nonexpert (ART-Pro-2) radiologists for the detection of GG ≥2 csPCa
*Secondary objectives*
1. Evaluate if RSIrs plus axial *T_2_*-weighted MRI is noninferior to mpMRI among expert and nonexpert radiologists for the detection of GG ≥2 csPCa a
2. Compare quantitative RSIrs (objective interpretation) with qualitative mpMRI (subjective radiologist interpretation) for the detection of GG ≥2 csPCa a
3. Evaluate bpMRI, mpMRI, and RSIrs for avoidance of unnecessary biopsies (ie, any biopsy resulting in no cancer or only GG 1) a
4. Evaluate bpMRI, mpMRI, and RSIrs for the detection of GG ≥3 cancer
5. Assess performance of the above MRI techniques for the detection of each: GG 1 (overdiagnosis), GG 2, GG 3, and GG 4–5
6. Evaluate the quality of scan images: a. Percentage of cases with diagnostic quality imaging as per PI-QUAL b. Percentage of cases with moderate or severe distortion i. Percentage of cases where distortion correction is useful
7. Evaluate csPCa detection by targeted vs systematic biopsy cores
8. Measure inter-reader reliability of bpMRI and mpMRI
9. Evaluate accuracy of radiologists’ and RSIrs-based estimates of overall probability of csPCa on biopsy
10. Assess influence of RSIrs on bpMRI interpretation

bpMRI = biparametric MRI; csPCa = clinically significant prostate cancer; GG = grade group; mpMRI = multiparametric MRI; MRI = magnetic resonance imaging; PI-QUAL = Prostate Imaging Quality; RSIrs = Restriction Spectrum Imaging restriction score.

a Key secondary objectives.

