**Fig. 1 f0005:**
[figure not shown]
In ART-Pro-1, patients with suspected clinically significant prostate cancer (csPCa) undergo MRI, with images interpreted independently by two expert radiologists. Radiologist 1 provides a research report using only biparametric MRI (bpMRI; no contrast) and then a second research report after reviewing the dynamic contrast-enhanced images (full multiparametric MRI [mpMRI]). Radiologist 2 provides a research report using bpMRI plus Restriction Spectrum Imaging restriction score (RSIrs). After both radiologists have submitted their research reports, they are given each other’s results. They may review all images and discuss the case, if useful. Radiologist 1 submits a final clinical report to the patient’s medical record to guide biopsy decisions. MRI = magnetic resonance imaging; w/ = with; w/o = without.

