### Image distribution and processing

3.4

Images from within each institution’s health IT network are transmitted from their scanner(s) to a processing/routing system created for ART-Pro. This system creates and processes two subsets of images, one for reader 1 and one for reader 2. The subset for reader 1 includes the standard of care mpMRI sequences (DWI, T2W, and DCE). These images are fully identifiable with the patient ID and are no different from standard of care images when sent to PACS. The subset for reader 2 includes bpMRI (without DCE) and RSIrs; these are deidentified and assigned an anonymized ID before being sent back to PACS. This deidentified work list for reader 2 ensures that reader 2 does not inadvertently view the full set of mpMRI images and/or interfere with reader 1’s clinical work list essential for clinical reporting. The processing system generates RSIrs maps using the internal MATLAB code developed by the investigator team and described previously [27], [28], [34], [35]. Briefly, the multidirection (tensor), multi-*b*-value diffusion-weighted images are corrected for image distortions arising from *B_0_*-field inhomogeneity, gradient nonlinearity, and eddy currents. Background noise and receiver coil bias are then removed. The corrected data are fit to a multicompartment RSI model, and the signal from the slowest diffusion compartment is normalized by the median signal within the prostate on the *b* = 0 s/mm^2^ images to generate RSIrs maps. RSIrs maps from both short TE scans are averaged together to generate the final RSIrs map that is distributed to the radiologists.

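### The comparison labelled reader 2 bpMRI versus reader 1 mpMRI tests bpMRI plus RSIrs, so it can neither support nor refute noninferiority of bpMRI alone

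*Protocol article*

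**What the plan says.** The first primary objective in Table 1 (section 2.2) is: "Evaluate if bpMRI is noninferior to mpMRI among expert (ART-Pro-1) and nonexpert (ART-Pro-2) radiologists for the detection of GG ≥2 csPCa". RSIrs is not part of the test named there.

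Section 4.1.1 examines that noninferiority question with one-sided tests of sensitivity and specificity for two pairs of readings: "reader 1 bpMRI versus reader 1 mpMRI and reader 2 bpMRI versus reader 1 mpMRI". The significance level is 0.05 throughout.

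The two readers work from different material:

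- **Reader 1** (section 3.5.1): "Reader 1 is first blinded to the DCE sequence and reports the MRI using only the biparametric (T2W and DWI) sequences". That report is then locked, DCE is shown, and a second report is made.
- **Reader 2** (sections 3.4 and 3.5.2): "The subset for reader 2 includes bpMRI (without DCE) and RSIrs", and "reader 2 completes a separate research report using bpMRI and RSIrs". The legend to Figure 1 says the same.
- **Reader 2's scoring** (section 3.5.2): "Lesions are assessed according to PI-RADS v2.1 with bpMRI; additionally, reader 2 reports the maximum RSIrs for each lesion".

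Section 4.2, on ART-Pro-2, numbers bpMRI and RSIrs plus bpMRI as two separate approaches, (1) and (4).

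**The concern.** A comparison offered as evidence on bpMRI should differ from mpMRI only by the missing contrast series. Reader 1's pair does. The second pair changes three things at once: DCE is taken away, RSIrs is added, and another radiologist reads.

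The article itself expects RSIrs to matter. The Introduction cites retrospective work suggesting that RSI makes cancers more visible and improves radiologist accuracy. Secondary objective 10 is to assess how RSIrs influences bpMRI interpretation.

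At stake is the trial's main message. Section 5 says that patients could be spared contrast if bpMRI proves noninferior. Centres without RSI could take a favourable reader 2 result as support for plain bpMRI when RSIrs supplied part of the sensitivity. The error can also run the other way: an unfavourable result could reflect disagreement between two radiologists and not the loss of contrast.

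**Working it through.** **1. What each comparison changes**

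| | Reader 1 bpMRI vs reader 1 mpMRI | Comparison labelled reader 2 bpMRI vs reader 1 mpMRI |
|---|---|---|
| DCE | removed | removed |
| RSIrs | absent from both | present in the first reading only |
| Radiologist | same | different |
| bpMRI score locked before further images | yes (3.5.1) | no such step described (3.5.2) |

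Only the first column isolates the effect of contrast.

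**2. The plan's own figure**

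Inputs from section 4.1.2 (sensitivity): margin m = 0.08; true difference 0; probability that the first test is positive and the second negative, p10 = 0.05; n = 145; at least 80% power. The level is one-sided 0.05 (section 4.1.1). A zero difference gives p01 = 0.05, so total discordance is 0.10. The same inputs are used for both comparisons.

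- Wald sample size: (1.645 + 0.842)² × 0.10 / 0.08² gives 97 after rounding up.
- Restricted-maximum-likelihood score test: 119.
- Power at n = 145: 0.87 (score, asymptotic) or 0.89 (score, exact enumeration).

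The statement of at least 80% power is met. The number 145 is close to 500 × 0.30 × 0.97 = 145.5. The point here concerns what is tested, so no corrected sample size follows from it.

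**3. Illustration of possible misattribution**

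Keep n = 145, m = 0.08, one-sided 0.05 and p10 = 0.05. For a true net loss L of the first reading, p01 = 0.05 + L. The Wald approximation to the probability of passing is

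Φ[(m − L) / √((p10 + p01 − L²)/n) − 1.645].

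- L = 0.05: variance 0.15 − 0.0025 = 0.1475; standard error √(0.1475/145) = 0.0319; 0.03/0.0319 − 1.645 = −0.70; probability 0.24.
- L = 0.03: variance 0.13 − 0.0009 = 0.1291; standard error √(0.1291/145) = 0.0298; 0.05/0.0298 − 1.645 = 0.03; probability 0.51.

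By exact enumeration:

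| True net loss | Score test | Wald test |
|---|---|---|
| 8 points | 0.05 | – |
| 5 points | 0.23 | 0.25 |
| 3 points | 0.48 | 0.52 |
| 0 points | 0.89 | – |

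As an example, suppose bpMRI alone loses 8 points. The reader 1 comparison then passes 5% of the time. If RSIrs gives back 3 points (net loss 5), the comparison labelled reader 2 bpMRI passes 23–25% of the time; if it gives back 5 points (net loss 3), 48–52%. The 8-point loss and both gains are assumptions.

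**4. Effect of the second radiologist**

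Two radiologists may disagree more often than one radiologist with himself or herself. With a zero true difference and n = 145, exact score power falls from 0.89 at 5% discordance each way to 0.80 at 7% and 0.72 at 9%. The 7% and 9% are assumptions. A failed reader 2 comparison would therefore not show that bpMRI is worse.

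**The case against.** **RSIrs as an add-on.** Section 3.5.2 ties reader 2's PI-RADS score to bpMRI and records RSIrs as an additional item, and section 4.3 treats both readers as having bpMRI PI-RADS scores. The reader 2 form is in a supplement that is not shown. A reader might infer that no bpMRI-only score from reader 2 exists at all. The article does not prove that; it shows only that none is described. This part stands and the fix allows for it. But naming the scoring system does not blind a reader to maps supplied in the same image set.

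**The contrast is intended.** The article says more than once that it will test avoiding contrast with or without RSIrs. Section 5 poses separate questions: whether contrast can be avoided, and whether RSIrs helps to avoid it. Section 4.1.1 covers primary and key secondary objectives and never calls the reader 2 comparison primary. All of this supports keeping the analysis. It does not support its label or its place under the bpMRI question.

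**Two routes to one claim.** A reader might infer that success on either comparison would establish bpMRI noninferiority. No such rule is stated, and p values are to be reported for every test, so a failing reader 1 result would stand beside a passing reader 2 result.

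**The illustration is not an error rate.** If bpMRI plus RSIrs truly loses only 3 to 5 points, passing is a correct result for that reading. It misleads only when it is credited to bpMRI alone. This stands.

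**Conclusion.** The point holds in a limited form. As described, the second comparison measures bpMRI plus RSIrs in another radiologist's hands against reader 1's mpMRI. It is mislabelled and misplaced as a test of bpMRI. This rests on three descriptions of reader 2's material that agree with one another, on the absence of any described RSIrs-blinded score, and on the article's own separation of the two approaches in ART-Pro-2.

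The trial keeps a sound ART-Pro-1 test of its primary question, the locked within-reader comparison of reader 1, and its design and sample size are untouched. The documents therefore support a risk of misattribution and not a forecast that it will happen. Nor do they supply a size: the pass rates above depend on an assumed bpMRI loss and assumed RSIrs gains.

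**What to change.** 1. In section 4.1.1, relabel the second comparison as reader 2 bpMRI+RSIrs versus reader 1 mpMRI. List it as a secondary analysis of whether RSIrs facilitates omission of contrast.
2. Add that objective to Table 1. The nearest entries are secondary objective 1 (RSIrs with axial T2W images) and objective 10 (influence of RSIrs on bpMRI interpretation); neither is this noninferiority comparison.
3. State that the ART-Pro-1 primary bpMRI conclusion rests on reader 1 bpMRI versus reader 1 mpMRI alone.
4. In section 4.3, label the reader 1 versus reader 2 kappa for PI-RADS as bpMRI versus bpMRI+RSIrs.
5. If the reader 2 form does record a bpMRI score before RSIrs is seen, say so and use that score wherever reader 2 bpMRI is named.

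No cross-stage test is needed. Section 4.2 already plans an expert bpMRI versus mpMRI analysis as a validation. Setting ART-Pro-2 expert bpMRI reads against ART-Pro-1 reader 1 mpMRI would keep the different-reader problem and favour reader 1, whose final report guides biopsy.

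The cost is a few changes of wording and one added objective. No new patients or reads are required. The changes should be made before the outcome data are analysed.

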#### Sample size calculations

4.1.2

All power calculations are conducted using software PASS 14.0.9 and R 4.3.1, unless otherwise indicated.

For testing the sensitivity, we expect the sensitivity to be 90% from the second test in each of the paired comparisons (reader 1 mpMRI), and assume a margin of 8% in defining noninferiority and an actual difference of 0%. We expect the percentage of probability of the first test giving a positive result while the second giving a negative result will be 5%. A sample size of 145 patients achieves at least 80% power at significance level 0.05. We plan to enroll 500 patients and expect that 30% will be diagnosed with csPCa, yielding 175 analyzable patients for the evaluation of sensitivity. Given the design of the trial, missing data are expected to be low (3%). Therefore, with the proposed sample size, we will have ample power in the above statistical tests.

For testing the specificity, we expect the specificity to be 40% from the second test in each of the paired comparisons, and assume a margin of 10% in defining noninferiority [42] and an actual difference of 0%. We expect the percentage of probability of the first test giving a negative result while the second giving a positive result will be 5%. Of 500 patients enrolled, 350 are expected to not be diagnosed with csPCa (either no biopsy due to low clinical/imaging risk or biopsy negative for csPCa), with a missing data rate of 3%. A sample size of 340 analyzable patients achieves at least 80% power at significance level 0.05.

For testing the noninferiority of the ROC curves associated with RSIrs and mpMRI, a preliminary study of 476 patients indicates that the AUC of the model with RSIrs is 0.747 (95% confidence interval [CI]: 0.7025–0.7884), while the AUC of the model with mpMRI is 0.767 (95% CI: 0.726–0.8085). With the proposed sample size, we will have at least 80% power in the noninferiority test with a margin of 8%. The power analysis is conducted with R 4.3.1 and package pROC.

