### Analyses for ART-Pro-2

4.2

Statistical analyses for ART-Pro-2 will be analogous to those described for ART-Pro-1. In ART-Pro-2, each radiologist will give sequential reports on each assigned patient case, that is, either (1) bpMRI and (2) mpMRI or (3) RSIrs plus T2W axial, (4) RSIrs plus bpMRI, and (5) RSIrs plus mpMRI. We will compare each approach (1 and 3–5) to mpMRI in an analogous manner to that in ART-Pro-1 using McNemar’s test and AUCs. These analyses will be performed within each stratum of ESUR radiologist expertise, testing for noninferiority compared with mpMRI PI-RADS for ESUR-defined experts (essentially a validation of ART-Pro-1), radiologists with basic prostate MRI proficiency, and novices. In terms of statistical power, each of these ART-Pro-2 subgroups will have the same statistical power as the primary and key secondary analyses of ART-Pro-1.

Additionally, we will estimate the effect of radiologist expertise for each approach (1–5) in linear mixed-effect models that utilize all the data from ART-Pro-2. Models will take the following form:csPCastatusscore+experience+(1|patient)+(1|radiologist)

Here, csPCa status is whether the patient was diagnosed with csPCa (binary), score is the PI-RADS or Likert score assigned, and experience is a categorical variable for ESUR/ESUI level of experience. Importance of radiologist experience within each approach (1–5) will be estimated by the parameter estimates for ESUR/ESUI basic proficiency and ESUR/ESUI novice levels, compared with a reference of ESUR/ESUI experts.

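### The primary noninferiority hypotheses carry a margin, but the test named for them, McNemar's, has none; the name conflicts with the stated null and with the power statement

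*Protocol article*

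**What the plan says.** Section 4.1.1 of the protocol article opens the primary analysis correctly: "we will conduct one-sided noninferiority tests of correlated proportions, to examine the sensitivity and specificity of the following paired readings". Two pairs are listed, reader 1 bpMRI against reader 1 mpMRI and reader 2 bpMRI against reader 1 mpMRI. The procedure follows: "A McNemar's test will be used to test the null hypothesis that the differences in the probabilities" of a positive MRI (sensitivity) or a negative MRI (specificity) "from the two readings in the paired comparison are larger than the predetermined noninferiority margins". The difference is taken as second test minus first, and section 4.1.2 identifies the second test as reader 1 mpMRI, so the null points the right way. On the level: "For all tests below, the significance level of 0.05 will be used in the statistical testing".

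Section 4.1.2 gives the margins, 8% for sensitivity and 10% for specificity, with a true difference of zero in both. For sensitivity, "we expect the sensitivity to be 90% from the second test in each of the paired comparisons", one discordant cell is put at 5%, and 145 patients are said to give at least 80% power. For specificity, the discordant cell is again 5% and the number is 340.

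Section 4.2 compares the ART-Pro-2 approaches with mpMRI "in an analogous manner to that in ART-Pro-1", naming McNemar's test again, within each expertise stratum and for noninferiority. Section 4.3 uses McNemar's test once more, for overdiagnosis rates, where no margin is given.

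**The concern.** The sentence in section 4.1.1 joins two things that do not go together. The null is that bpMRI falls short of mpMRI by more than a margin. The test named for it has the null that the two discordant probabilities are equal. Its statistic uses only the discordant counts; neither the margin nor the total number of patients enters it.

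The article writes out no margin-shifted statistic and no confidence-limit rule, so the test name is the only operational instruction for the primary analysis. A standard McNemar routine returns the equality p value without any warning that the margin has been left out. That p value answers a different question from the primary objective in Table 1. The same name then covers margin hypotheses in sections 4.1.1 and 4.2 and an equality comparison in section 4.3.

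**Working it through.** **Inputs (section 4.1.2, sensitivity).** n = 145, margin m = 0.08, true difference 0. Let p10 be the probability that bpMRI is positive and mpMRI negative, and p01 the reverse. The article gives p10 = 0.05; zero difference then implies p01 = 0.05. Counts are x (favouring bpMRI) and y (against it).

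**The two tests.**
- Ordinary McNemar, null p10 = p01: z = (x − y)/√(x + y).
- Margin test, null p10 − p01 = −m: z = (x − y + n·m)/√v, with v = n·[2q − m(1 + m)]. Here q is the estimate of p01 restricted to the null (the Nam/Tango restricted score test).

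**Does the plan's own figure fit a margin test?** The simple Wald formula at one-sided 0.05 and 80% power gives n = (1.645 + 0.842)² × 0.10/0.08² ≈ 97. Exact enumeration of the discordant counts for the score test at n = 145 gives 88.6% power at one-sided 0.05 and 80.5% at one-sided 0.025. The claim of at least 80% is therefore met by a margin-based paired test at either level. For specificity (n = 340, margin 0.10, 5% each way) the power is above 99.9%.

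**Does it fit ordinary McNemar?** With p10 = p01 = 0.05, McNemar's null is true. By the same enumeration, the one-sided test at 0.05 rejects in favour of bpMRI in 5.0% of trials at n = 145, and in 5.0% at n = 340. No sample size lifts this to 80%, because the assumed truth is the test's own null.

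**Single data sets at n = 145** (n·m = 11.6; McNemar p two-sided, margin p one-sided):

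| x vs y | McNemar | Margin test |
|---|---|---|
| 0 vs 6 | z = −6/√6 = −2.45, p = 0.014: bpMRI worse | q = 0.0800, v = 10.67, z = 5.6/3.27 = 1.71, p = 0.043: noninferior at 0.05 |
| 3 vs 9 | z = −6/√12 = −1.73, p = 0.083: not significant | q = 0.0947, v = 14.94, z = 5.6/3.87 = 1.45, p = 0.074: noninferiority not shown |
| 7 vs 7 | z = 0, p = 1.0 | q = 0.1092, v = 19.13, z = 11.6/4.37 = 2.65, p = 0.004: noninferior |

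The first row is a reversal. In the third, the readings are equally good, yet McNemar has nothing to report.

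**Conditional on a misreading.** Suppose someone took a nonsignificant two-sided McNemar result as noninferiority, a rule the plan does not state. At a true loss of exactly 8 points and n = 145, that rule would claim noninferiority in 8.4%, 23.0% and 34.9% of trials for (p10, p01) = (0.01, 0.09), (0.03, 0.11) and (0.05, 0.13). The margin test at one-sided 0.05 errs in 4.1%, 4.6% and 5.0%. Only the last pair keeps the article's 5% for p10; the other two are assumptions that show the range.

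**The case against.** The best defence is that the label is loose and everything else is right. Section 4.1.1 commits to one-sided noninferiority tests of correlated proportions and writes the margin into the null; section 4.1.2 gives the margins and a sample size that only a margin-based paired test can explain. On this view analysis and power share one margin test, casually called McNemar's. A source is cited at that very sentence; it cannot be seen here and may describe a margin-shifted variant. Section 4.2 then carries over the margin null along with the label.

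Most of this stands, and it limits the point. A reader might infer that the primary analysis cannot support noninferiority at all, or that the plan leaves the false-claim rate uncontrolled. The document supports neither. A p value for the null as written would serve, and nowhere does the plan treat nonsignificance as noninferiority or demand superiority. Nor does it restrict reporting to p values: it promises them for every test and does not rule out intervals.

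The defence does not remove the conflict. The article goes beyond leaving the statistic to a fuller plan: it names one for the primary objective, names it again for ART-Pro-2, and uses the same name in section 4.3 where an equality test would be proper.

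**Conclusion.** The point holds as a conflict between the named test and the stated hypothesis. Followed literally, McNemar's test neither tests the 8% and 10% margin nulls nor delivers the stated power: about 5% rejection in favour of bpMRI at zero difference, against 88.6% for a margin-based score test at one-sided 0.05 with 145 patients. It can also reverse the conclusion in a single data set. These figures rest on the article's 5% discordance, taken as equal in both directions because the assumed difference is zero, and on the ordinary form of McNemar's test.

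The hypothesis, its direction, the margins and the sample size are not in question. Because the conflict sits on the primary decision and is cheap to remove, it should be corrected before the analysis.

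**What to change.** - In sections 4.1.1 and 4.2, replace McNemar's test with a margin-based test for paired proportions at margins of 8% and 10%. The Nam/Tango restricted score test is one choice; the matching confidence limit of the paired difference, compared with the margin, is equivalent.
- State that noninferiority is concluded when that limit excludes the margin, and report the interval with each p value.
- Name the same test in section 4.1.2, so that power and analysis refer to one procedure.
- Keep ordinary McNemar for equality comparisons such as overdiagnosis in section 4.3, and say that no margin applies there.

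The cost is wording and a different software routine. The number of patients, the margins, the significance level and the data collected all stay as they are.
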